### Intervention

The intervention consists of 1) knowledge and skills training for mental health professionals of the CMH teams about DVA, 2) knowledge and skills training of DVA practitioners about mental illness, 3) the provision and implementation of a direct care pathway between CMH services and DVA services for victims of DVA with mental illness.
*Knowledge and skills training for mental health professionals about DVA:*

The training for the teams has been developed by the research team and is aimed at improving knowledge and skills regarding detection and management of DVA. At the start of the trial, all CMH teams in the intervention group will receive a training of approximately 8 hour in total, divided over 2 days. The topics covered in the training used in the LARA-intervention were included here [13] and consist of four main themes namely;Improving knowledge about DVA; (the definition and different forms of DVA; prevalence and incidence of DVA in the Netherlands; and symptoms and signals of DVA, including cultural differences in expression).Identifying and documentation of DVA when taking the patient’s history: this theme will cover different techniques a clinician can use to discuss and assess DVA with a patient and includes advice on how to document DVA.Safety: this theme entails safety assessment and management for patients and clinicians and will also include laws and legislation on DVA in the Netherlands.Treatment/follow up: this theme will discuss referral pathways and ways to empower/support patients who are victims of DVA.The training is modified according to the characteristics of the specific municipality. This means that the teams will receive training with a referral pathway adapted to the Rotterdam and The Hague municipality, respectively.

### Implementation

All members of a CMH team randomized in the intervention condition will be invited to attend the training. Attendance will be monitored. During, and after initial training, teams are actively encouraged to implement the techniques learned in their daily practice.

After the training, clinicians will receive an extended manual incorporating good practice guidelines and information on local/national DVA services. To improve implementation of the knowledge gained in the training, each team in the intervention condition will be recommended to assign a advocate on DVA. Advocates in the intervention teams will collect all problems and questions regarding DVA in their team. We will maintain close contact with the DVA advocates throughout the study through e-mail. Advocates can address problems in the collaboration with DVA practitioners and/or referral to DVA services to the DVA expert team in the institution. This expert team is not part of this study and is already in place at the two participating institutions before the beginning of this study. We will also hand out posters with conversational techniques on DVA and cards team members can use as an aid when talking to their patients about DVA.

The teams in the control condition will not receive any additional training in DVA. Clinicians in the control condition however, can refer patients to DVA services(according to standard practice), when they detect a patient suffering from DVA.2)
*Knowledge and skills training of DVA practitioners about mental illness:*

The professionals working at VT will be offered training on mental illness and procedures within mental health care. The training has been developed by the research team and can be adjusted according to the baseline level of knowledge of the professionals working at VT. Regardless of adjustment, the training consists of a the following key elements:Knowledge on mental illness (including conversational techniques and pitfalls and possibilities in dealing with psychiatric illness)Structure of mental health care services and patient-doctor confidentialityReferral to and communication with clinicians working in mental health care
3)
*The provision and implementation of a direct care pathway between CMH services and DVA services for victims of DVA with mental illness*

Our study will focus on providing professionals working in mental health care with the necessary skills refer victims of DVA to services specializing in DVA and to implement the Meldcode protocol as part of the referral pathway in daily practice. The Meldcode is explained in more detail in the section legislation. Professionals will be provided with a visual outprint of the Meldcode, contact information on local DVA services and information on resources on DVA in their own organization in the manual of the training. Every professional has access to a work related smartphone and professionals will be encouraged to install the Meldcode app.

### Outcome measures, aims and data collection

#### Primary outcome

The primary outcome measure is the rate of detected of DVA cases per CMH-team, taking into account the number of patients in each team. Outcomes will be obtained through a systematic search in electronic patient files at the participating mental health institutions. We will search the electronic patient files using a set of keywords, their synonyms, (miss-)spellings and words closely associated with DVA. Our main keyword will be domestic violence. This keyword will first be piloted and validated. A specialized software program will be used to analyze the information in the electronic patient files of the detected cases to determine words closely associated with domestic violence. To validate the detected cases, we will assess each detected case of DVA individually using information from the electronic patient file. Non-cases will be verified randomly. Reliability of the data extraction will be evaluated by repeating the data extraction on a subset of teams by a second independent researcher and compare the outcomes. To ensure comparability in timing, we will pair control and intervention teams and obtain outcome data simultaneously. We expect an underreporting of detected cases and over-reporting of referred cases by the clinicians in the patient records [30]. Since these biases will affect both intervention and control condition equally, study results will remain valid.

#### Secondary aims and outcomes

The BRAVE intervention has the following secondary aims and outcomes:

Aim 1 - to assess gains and sustainability in knowledge on DVA among mental health professionals.

Aim 2 - to assess the feasibility, sustainability and acceptance of the intervention among CMH teams and,

Aim 3 - to assess the (possible) referral pathway to DVA services and the implementation of the Meldcode.

We will assess Aim 1 using a structured questionnaire – The BRAVE Survey - developed specifically by the study team, to assess CMH teams knowledge and attitudes regarding DVA.

Aim 1 - the BRAVE survey

The BRAVE survey was informed by the PREMIS [37] and PROTECT questionnaires [38].

All members of the included teams will receive this survey. The survey has a total of 53 questions divided into 5 sections: (1) Respondent profile, (2) Previous Courses on DVA (3) Skills in management of DVA, (4) Knowledge on DVA and (5) Opinions on DVA. Section 1; “Respondent profile” consists of 7 questions, of which 3 are multiple choice and 4 questions an individual can fill in. Participants are asked about their professional background (work experience, current profession, educational level) and general information (date, age, gender); section 2; “Previous courses attended on DVA” consists of a multiple choice question about previous courses on DVA. If participants check yes they are asked 4 questions about duration of this course and when this course was completed. Section 3; “Skills in management of DVA” consists out of 7 multiple choice statements. Participants can check the box on the Likert scales, ranging from 1 (not skilled) to 5 (very skilled), the extent to which they feel skilled to handle/judge a particular described situation regarding DVA. Section 4; “Knowledge on DVA” consists of a total of 14 multiple choice statements. For the first three questions, participants need to check the box on Likert scales, ranging from 1 (nothing) to 5 (a lot). These questions are followed by 10 multiple choice questions with statements about DVA where participants can choose between true (1) and not true (2). The last question in this section asks the participants to combine the correct described statement with the right stage of the process of discontinuing a relationship with a perpetrator. Section 5; “Opinions on DVA” consists of 16 statements on DVA where participants can choose whether they agree on a Likert scale ranging from 1 (do not agree) to 5 (agree).

To be able to compare the scores of the survey, sections 3 (Skills), 4 (Knowledge) and 5 (Opinions) will be calculated separately per participant and will then be aggregated at a team level. Qualitative answers will be given a score and, post-hoc assigned to answering categories. Statistical comparisons will be made between intervention and control teams.

This questionnaire will be assessed at baseline, after 6 months of the intervention and after 12 months of the intervention.

We will assess Aim 2 by conducting semi structured in-depth interviews with members of CMH teams, policy makers, patients and DVA practitioners about the feasibility, sustainability and acceptance of the intervention.

Aim 2 Semi-structured in depth interviews

We will obtain outcomes regarding opinions on feasibility, sustainability and acceptance of the intervention using a semi-structured in depth interview with a purposive sample of professionals in the intervention - and control group, team-leaders, managers, patients in the intervention group, patients in the control group, patients who have experienced DVA and patients who didn’t experience DVA. The interview for clinicians will mostly focus on their opinions and personal definition of the following themes:DVAactions (not) takenreferral pathways between CMH services and DVA servicesimpact of the intervention on care provision and care professionals (including personal safety)impact of the intervention on client relationshipimpact of the intervention on client wellbeing (including personal safety)level of implementation of the intervention in daily practicefeasibility of implementation of the interventionsustainability of the intervention

In the policy makers of the included mental health institution and team managers the in depth interview will focus on their opinions and personal definition of the following themes:DVAthe interventionreferral pathways between CMH and DVA serviceslevel of collaboration between CMH and DVA servicesimpact of the intervention on care provision and operational capabilitycost-effectiveness of the intervention

The in depth interview with psychiatric patients will focus on their opinions and personal definition of the following themes:DVAdisclosure of DVAavailable help for DVA

We will gather data until saturation of the theoretical framework (what is the feasibility, sustainability and acceptance of the intervention as well as how was the intervention implemented). Interviews will be recorded and transcribed as preparation for analysis. We will analyze the data with a mix of content and framework analysis. After the frameworks are identified, the data will be structured, labelled and coded.

We will assess aim 3 using the detected cases from the primary outcome. We will then search electronic patient files of the detected cases to identify cases of DVA referred to professional DVA services per included CMH team.

Aim 3 Evaluation of the referral pathway to professional services on DVA of detected cases

Detected cases are extracted from the electronic patient’s files using the method described in the section ‘Primary outcome’ of this article. Of all detected cases of DVA the following information, will be extracted from the electronic patient file, when available: 1) the time from disclosure of DVA to referral, 2) details on any consultation with VT and/or colleagues, including the possible reason for consultation and advice given; 3) if the patient was involved in the decision to engage with VT and/or colleagues and their opinion about the given advice; 4) how the severity of the DVA case was assessed and which sources were used for the assessments; 5) details on the referral process, Including the reasons for the formal request for advice/ informal advice from VT, reasons for the ultimate decision to refer/not to refer, details of the referral site, the care provided at the referred institution, and outcomes for the patient with regards to the (ending of) violence. In doing so, we aim to assess the qualitative characteristics of the referral pathway in the intervention and control teams.

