#### Survey on knowledge and attitudes on DVA

Subscale scores from BRAVE survey will be calculated. For each participant change scores will be calculated between baseline and follow-up score. Generalized Estimating Equations analysis will be used to compare mean change score in the intervention and control teams. The CMH team will be included as a random effect to account for the clustering of the data. Questionnaires with more than 5% of the questions missing will be removed from the sample. Questionnaires with less than 5% missing will be imputed using multiple imputation.

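### The section 4 Knowledge score mixes apparent self-ratings with factual items, so a gain on Aim 1 could appear without any gain in factual knowledge

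*Protocol article*

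**What the plan says.** The relevant text is in the protocol article under Secondary aims and outcomes and under Survey on knowledge and attitudes on DVA.

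- **The aim:** "Aim 1 - to assess gains and sustainability in knowledge on DVA among mental health professionals".
- **The items:** Section 4 of the BRAVE survey has 14 items of three kinds. First come the ratings: "For the first three questions, participants need to check the box on Likert scales, ranging from 1 (nothing) to 5 (a lot". Next come the factual statements: "10 multiple choice questions with statements about DVA where participants can choose between true (1) and not true (2". Then there is one matching task: "The last question in this section asks the participants to combine the correct described statement with the right stage".
- **The scoring unit:** "sections 3 (Skills), 4 (Knowledge) and 5 (Opinions) will be calculated separately per participant". These scores are then aggregated by team and compared between arms.
- **The analysis:** "Subscale scores from BRAVE survey will be calculated", and "For each participant change scores will be calculated between baseline and follow-up score". Mean change is compared between arms by generalized estimating equations.
- **Timing and setting:** The survey is given at baseline, 6 and 12 months. Randomization and blinding says that team professionals cannot be blinded. Intervention describes about 8 hours of training for intervention teams, and Implementation says that control teams get no additional training.

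**The concern.** Section 4 is the only part of the survey that tests facts. How skilled staff feel in handling situations is already covered by section 3, which has its own score. Placing three ratings anchored at nothing and a lot inside the Knowledge section brings perception back into the one score that should measure knowledge.

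The two kinds of item need not move together. Staff who have just taken a course, and who know they are in the intervention arm, may rate themselves higher whatever they retained. Control staff have no such prompt. The difference in change scores between arms would then combine a factual effect and a perception effect, and the section score cannot tell them apart.

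Both halves of Aim 1 are exposed. A gain might be partly or wholly perceived. A score still above baseline at 12 months might reflect confidence that lasted after the facts were forgotten.

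**Working it through.** **Inputs, all from the description of section 4 under Secondary aims and outcomes**

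- Ratings: 3 items, each 1 to 5.
- True/not-true: 10 items, two options each.
- Matching: 1 item. Its points are not stated, so its range is called k and taken as 0 to 7 by assumption.

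**Step 1. Reproduce the item count.** 3 + 10 + 1 = 14, as stated. The three kinds of item make up the whole section.

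**Step 2. Range of each part, if items are summed raw (an assumption).**

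- Ratings: 3 × (5 − 1) = 12 points.
- True/not-true: 10 × 1 = 10 points. This holds whether responses are coded 1/2 or scored 0/1.

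**Step 3. Share of the range held by the ratings:** 12 / (12 + 10 + k).

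| Matching item, k | Total range | Share of ratings |
|---|---|---|
| left out (0) | 22 | 54.5% |
| 1 | 23 | 52.2% |
| 2 | 24 | 50.0% |
| 3 | 25 | 48.0% |
| 5 | 27 | 44.4% |
| 7 | 29 | 41.4% |

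If every item is instead rescaled to 0–1, the share is 3/14 = 21.4%.

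**Step 4. What a shift in self-perception alone would do.** Let each rating rise one step, with no factual answer changed.

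- Raw sum: 3 × 1 = 3 points, the same as three more correct true/not-true answers. This is 3/22 = 13.6% of the range without the matching item and 3/27 = 11.1% at k = 5.
- Every item rescaled to 0–1: 3 × 1/4 = 0.75 points, the same as three quarters of one correct answer, or 0.75/14 = 5.4% of the range.

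The size depends on the combining rule. A score gain without factual gain is possible under either.

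**Step 5. Sustainability.** In a raw sum, losing three correct answers between 6 and 12 months would be exactly offset by one step up on each rating. Ratings that merely stay level would not hide such a loss in points, but they would keep the score above baseline after the factual gain had gone.

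**The case against.** The strongest objection is that the article states no combining rule. It speaks of section and subscale scores without saying whether items are summed, averaged or rescaled, and it does not exclude subscales within section 4. A condensed article commonly leaves item scoring and answer keys to a fuller document. That stands as far as the missing detail goes, and the missing detail is not the point here. What the article does state is that the section is the unit of scoring, and it describes section 4 as one section with mixed content.

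Three stronger readings are tempting, and the documents do not support them.

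- **Self-perception makes up more than half of the score.** This needs a raw sum and a matching item spanning fewer than 2 points, and neither is stated. The share falls to 21.4% under rescaling.
- **Self-ratings supply most of the score's variance.** Assume a rating SD of 1, correlation r between ratings, proportion correct p, and correlation ρ between factual items, and leave the matching item out. The share is then (3 + 6r) / [3 + 6r + 10p(1 − p)(1 + 9ρ)]. With ρ = 0 it runs from 3/5.4 = 56% (r = 0, p = 0.6) to 6/7.6 = 79% (r = 0.5, p = 0.8). With ρ = 0.2 and p = 0.6 it is 3/9.72 = 31% (r = 0) or 6/12.72 = 47% (r = 0.5). No figure in the article decides between these.
- **The printed codes 1 and 2 would be summed without an answer key.** They are described as response options, not as a scoring rule. Nothing shows that correctness would be ignored.

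It is also fair to say that the wording of the three rated items is not given. Calling them self-ratings is an inference from their anchors, though a strong one. Finally, the items remain separable in the data, and the primary outcome, extracted from patient files by a researcher blinded to allocation, is unaffected.

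**Conclusion.** The point holds in a limited form. As written, the plan scores section 4 as one Knowledge score although it mixes apparent self-ratings with factual items. With unblinded staff and training in one arm only, that score can rise or be sustained through perception without a factual gain, so the conclusion on Aim 1 would not follow from it alone. This is a possibility built into the measure, not a prediction that it will occur.

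The size is open. Under a raw sum the ratings span 12 points against 10 for the true/not-true items. Their share of the full range is between 41.4% and 54.5% for k from 7 down to 0, and 21.4% if all items are rescaled. The conclusion does not depend on which of these applies. It rests on two readings: that the three items are self-ratings, and that one score per section means no split within section 4. It is an inexpensive improvement to a secondary aim.

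**What to change.** Amend the scoring text under Secondary aims and outcomes and under Survey on knowledge and attitudes on DVA, before the survey data are analysed:

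1. Define the factual knowledge score as the ten true/not-true items plus the matching item, marked correct or incorrect against an answer key, and state the points for the matching item.
2. Report the three 1-to-5 items as a separate perceived-knowledge score.
3. Base the Aim 1 statement on gain and sustainability of knowledge on the factual score. Present perceived knowledge beside it.

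The cost is a change of wording, one more subscale to report, and a shorter knowledge score of 11 items instead of 14. No further data collection is needed.

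### Equal over-reporting in both arms does not make the Aim 3 referral results valid, and the direction of the bias depends on how referral is measured

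*Protocol article*

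**What the plan says.** Under Secondary aims and outcomes, the protocol article starts from the cases detected for the primary outcome and identifies referrals per team from the same source: "We will then search electronic patient files of the detected cases to identify cases of DVA referred to professional DVA services". The stated purpose is that "we aim to assess the qualitative characteristics of the referral pathway in the intervention and control teams".

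Under Primary outcome, it states what it expects of that source: "We expect an underreporting of detected cases and over-reporting of referred cases by the clinicians in the patient records". It then concludes: "Since these biases will affect both intervention and control condition equally, study results will remain valid".

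The quality checks in that section stay within the file. One is "To validate the detected cases, we will assess each detected case of DVA individually using information from the electronic patient file". Another is "Reliability of the data extraction will be evaluated by repeating the data extraction on a subset of teams by a second independent researcher". Non-cases are checked at random. All three concern detection or extraction. No comparison with the records of Veilig Thuis (VT) or another domestic violence service is described.

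Under Intervention, the training given to intervention teams alone covers referral pathways and "includes advice on how to document DVA".

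**The concern.** The protocol names an error in its source, uses that source for an outcome, and sets the error aside because it is the same in both arms. For over-reported referrals, sameness is not enough. A file that records some referrals that did not take place overstates referral in each arm, and the comparison between arms is generally distorted as well.

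The direct referral pathway is the third component of the intervention, and more referral is part of the trial's rationale. At stake is what can be said about Aim 3: how often detected cases were referred, and whether that differed between arms. A reader who relies on the validity sentence would take both at face value.

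**Working it through.** The protocol gives no referral rate and no rate of over-reporting, so there is no figure to reproduce. The check asks whether equal error leaves the referral results intact.

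**Inputs from the protocol article (Sample size):** 12 teams per arm, 200 patients per team, 0.25% detected in control teams, 3.55-fold increase. They serve only to set a scale.
- Patients per arm: 12 × 200 = 2400
- Detected, control: 2400 × 0.0025 = 6.0
- Detected, intervention: 6.0 × 3.55 = 21.3

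**Assumptions, not in the protocol:** true referral among detected cases p = 10% control and 40% intervention; a share f of non-referred cases is noted as referred, equal in both arms, from 0 to 0.30; every true referral is noted.

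**1. Share of detected cases referred.** Observed share q = p + f(1 − p). Hence q₁ − q₀ = (1 − f)(p₁ − p₀), and the ratio moves towards 1.

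| f | Control | Intervention | Difference (points) | Ratio |
|---|---|---|---|---|
| 0 | 10% | 40% | 30 | 4.0 |
| 0.10 | 19% | 46% | 27 | 2.4 |
| 0.20 | 28% | 52% | 24 | 1.9 |
| 0.30 | 37% | 58% | 21 | 1.6 |

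**2. Number of referrals, the per-team reading.** Observed count = D × q, with D the detected cases per arm.

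| f | Control | Intervention | Difference | Ratio |
|---|---|---|---|---|
| 0 | 6 × 0.10 = 0.60 | 21.3 × 0.40 = 8.52 | 7.92 | 14.2 |
| 0.20 | 6 × 0.28 = 1.68 | 21.3 × 0.52 = 11.08 | 9.40 | 6.6 |
| 0.30 | 6 × 0.37 = 2.22 | 21.3 × 0.58 = 12.35 | 10.13 | 5.6 |

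The change in the difference is f × [D₁(1 − p₁) − D₀(1 − p₀)] = f × (12.78 − 5.40) = 7.38f. It is positive because the arm with more detected cases has more non-referred cases to mislabel. Per team (divide by 12), the difference goes from 0.66 to 0.78 at f = 0.20. The ratio still falls.

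**3. Over-reporting proportional to true referrals.** With an assumed factor of 1.5, the shares become 15% and 60%. The ratio stays at 4.0, but the difference rises from 30 to 45 points and both levels are wrong.

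**4. Unequal over-reporting (share of detected cases).**
- f = 0.20 control, 0.05 intervention: 28% and 0.40 + 0.05 × 0.60 = 43%, difference 15 points
- f = 0.05 control, 0.20 intervention: 0.10 + 0.05 × 0.90 = 14.5% and 52%, difference 37.5 points

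The true difference is 30 points, so the bias can go either way.

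**5. No true difference.** If p₀ = p₁, equal f gives q₀ = q₁. No false difference arises in the share referred.

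**The case against.** Four points can be made for the protocol.

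- **Aim 3 is secondary and described as qualitative.** The Statistical methods section gives models for detection and for the survey, none for referral. With about 6 detected control cases on the planning figures, a shift from 30 to 24 points would be lost in sampling error. This stands and sets the severity. It does not rescue the validity sentence, because referred cases are still to be identified per team in both arms and their levels would be overstated.
- **Much of the evidence is already to be collected.** The Aim 3 extraction covers VT consultation and its advice, the referral site, care given there and patient outcomes, where available. This also stands. A reader might infer that referrals which never arrived would be presented as care received. The protocol does not support that, because care received is extracted as a separate item.
- **The direction of bias is not fixed.** A reader might infer that false referrals always shrink the contrast, so that a working pathway would look weak. That holds for the share of detected cases under an equal false-positive rate. It fails for the difference in counts per team (step 2), and proportional over-reporting leaves the ratio unchanged (step 3). The protocol gives only the direction of the reporting error, neither its size nor its form.
- **Confirmation in the file has its own bias.** Intervention teams alone are trained in documentation and the pathway, so they may file feedback more often for the same true referral. This stands, and it rules out making confirmed referral the only referral outcome.

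**Conclusion.** The concern holds for referrals. The statement that results remain valid because the bias is equal is not supported for Aim 3:

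- Referral levels are overstated in both arms under every form of over-reporting considered.
- With an equal false-positive rate, the share of detected cases referred is pulled towards no difference (30 to 24 points, ratio 4.0 to 1.9 at f = 0.20), while the difference in counts is inflated (7.9 to 9.4 per arm).
- Equality of the bias is asserted, not shown, and the training gives a reason to doubt it.

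The sizes are illustrative. They rest on assumed referral shares, an assumed f and full recording of true referrals; the count figures also rest on the planning rates for detection.

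A reader might go further and infer that the trial's main result is compromised. The argument here concerns referrals only and leaves the primary outcome, detection, untouched. Severity is minor.

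**What to change.** 1. Under Primary outcome, limit the validity sentence so that it does not cover referrals. State that referral as noted in the file overstates true referral, and that the direction of bias in the arm contrast depends on the measure.
2. In the Aim 3 file review already planned, code each referral as confirmed (a VT report, an intake, returned advice or care provided is in the file) or as clinician note only.
3. Report both categories side by side by arm, per team and as a share of detected cases. Neither should be the sole referral outcome.

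The cost is one extra code on the extraction form, a few more table columns and a wording change. The drawback is that confirmed referral misses cases where no feedback was filed, possibly to a different extent in the two arms. The report should say so.
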